**Intervention: training program**

Phase II of the cardiac rehabilitation program will be based on the F.I.T.T.^32,33^ model, where the main parameters are the frequency of training, the intensity of the exercise, the duration of the sessions / complete program, and the type of exercise proposed:

- FREQUENCY. 2 sessions per week in a cardiac rehabilitation gym. In addition, the work will be complemented with a pattern of home exercise.

- INTENSITY. Intensity based on maximum oxygen consumption (VO2) and maximum heart rate (HR), calculated based on the ergospirometric tests performed. The Training HR (FCE) will be that given by the ventilatory thresholds obtained in the Wasserman curves.

- TIME. The sessions will last approximately 60 minutes (approximately 40 minutes of them correspond to the training phase). The program will include a total of 20 sessions (2 sessions a week for approximately 10 weeks).

- TYPE. The type of work indicated in cardiac rehabilitation programs in the aerobic phase will be the continuous and interval modality, which will be established depending on the risk stratification of the patient.

All patients will be monitored through a heart rate and O2 saturation recognition device. In addition, the patient's subjective perception of effort will be monitored at all times using the modified Borg Scale, both at the level of dyspnea and lower limb fatigue.

The sessions will be structured as follows:

Warm-up Phase (10 minutes):

- Respiratory exercises: Diaphragm + respiratory muscles training

- Low-intensity walking

Training Phase (40 minutes):

- Aerobic Exercise Phase on treadmill / cycle ergometer (20 minutes)

- Strength Exercise Phase (20 minutes) (Annex II)

Cooldown Phase (10 minutes):

- Low-intensity walking

- Stretching

**Outcome measures:**

Sociodemographic variables: age, sex, educational level, type of work, marital status, time spent with the partner.

Dependent and independent variables:

The evaluation of these variables will be carried out in conjunction with the cardiology service of the IMED Valencia Hospital. At the Hospital IMED, tests related to the patient's risk stratification (ergospirometry, echocardiography and biochemical profile) will be performed, and at CEU Cardenal Herrera University the patient's respiratory and functional capacities will be evaluated (pressure measurement, incremental Shuttle test, evaluation of strength, functional parameters of the lower limb), in addition to quality of life and sexual dysfunction questionnaires.

All variables will be evaluated at 3 different times: pre-intervention, immediate post-intervention and one year follow-up.

- Cardiology Service (Hospital IMED Valencia):

- Cardiopulmonary exercise testing (CPET), evaluated by ergospirometry. The stress test with oxygen consumption consists of subjecting the patient to physical exercise with a controlled and progressive workload, taking measurements before, during, and after carrying out said work, and subsequently analyzing the data obtained . This test provides us with information about their cardiac, pulmonary, musculoskeletal function, and the response of all of them to physical exercise, constituting essential information for a correct evaluation of the patient's situation, establishment of a prognosis, and a good point of evaluation. Departure for the design of cardiac rehabilitation programs in the population after acute myocardial infarction. Among the necessary equipment, a cycle ergometer / treadmill is essential, as well as measurement and analysis equipment, such as a cardiopulmonary exercise tower, metabolic cart, electrocardiogram, pulse oximeter, blood pressure monitor, and additional equipment (resuscitation cart, stretcher of examination, oxygen bullet) and accessories^34^.
- Ejection Fraction, measured by echocardiography. Ejection fraction is defined as the stroke volume divided by the ventricular volume at the end of diastole. In the left ventricle, it usually has a value of about two-thirds (55 to 65%). In patients who have suffered an acute myocardial infarction, the ejection fraction serves as an indicator of risk, along with other elements. Thus, the patient's risk can be stratified into Low, Medium and High.
- Biochemistry. Cardiac markers are used during the first hours for the diagnosis and evaluation of myocardial damage secondary to an AMI. In addition to the evaluation of these markers, numerous parameters can be altered in a patient with cardiovascular risk factors, such as in those with a history of dyslipidaemia or diabetes. Standard follow-up of patients includes biochemical analysis of triglyceride levels, total cholesterol, HDL and LDL cholesterol, and glycosylated hemoglobin. This study will also include inflammation markers such as C-reactive protein and interleukin 6, and NT-proBNP in those patients with associated heart failure. Likewise, iron metabolism parameters (serum iron, ferritin, transferrin saturation index, serum transferrin) will be included.

- Rehabilitation Service (CEU Cardenal Herrera University):

- Incremental Shuttle Walking Test (ISWT). It is a test derived from the "20-meter Shuttle run test" adapted to cardiac patients, such as those with coronary heart disease. The ISWT has demonstrated its effectiveness in the field of cardiac rehabilitation, in addition to being correlated with the maximum VO2 and metabolic equivalents of the cardiovascular patient. The patient must walk between two marks 9 meters apart, progressively increasing their speed^35-37^.

Functional capacities:

- 30 ’’ stand to sit test. It measures the maximum number of squats the patient is capable of performing in 30 seconds. The objective is to assess muscular endurance and rapid changes between concentric and eccentric contraction of the lower limb muscles. From a sitting position, the patient fully sits up in a standing position and returns to a full sitting position as many times as possible in the established time^38^.
- Monopodal quarter squat. The subject is asked to flex the knee in single leg stance. The evaluator scores performance as defined by Comerford and Motram^26,39^.
- Strength of hip extensors. It will be done using a hand-held dynamometer, carrying out 3 measurements of a concentric isometric contraction^38,40^.
- Chester Step Test. In this submaximal test, the patient must go up and down a step to the rhythm of a metronome, progressively increasing the speed. The height of the step will depend on the age and previous physical activity of the subject. This test has proven to be a good indicator of cardiovascular risk factors and a predictor of cardiovascular risk^41,42^.
- Maximum static inspiratory pressure (PIM, cmH2O) / Maximum static expiratory pressure (PEM, cmH2O), or maximum positive and negative pressure, respectively, that can generate and maintain the entire respiratory musculature, against an occluded circuit, for at least one 1 second^43^. It is determined at or near total lung capacity and residual volume^44^. A minimum of 3 measurements are made, 1 minute apart, and the highest value of the 3 extracted is selected for the results. The MicroRPM device (Carefusion, U.K.) will be used.

- Nursing Service (CEU Cardenal Herrera University):

- EuroQol (EQ-5D). It consists of two parts. The first corresponds to the description of the state of health in five dimensions (mobility, personal care, daily activities, pain / discomfort and anxiety / depression). In the second part of the questionnaire, the subject must score on a millimeter visual analog scale of their health status at the time they self-classify or self-perceive their personal status, having at the ends of the scale the worst health status (0) and the better health (100)^45^.
- The self-administered Sexual Health Inventory for Men questionnaire, validated and consisting of 5 items, will also be used in this study. This questionnaire is an abbreviated version of the International Index of Erectile Function Test and assesses erectile dysfunction in men^46^.

STATISTICAL ANALYSIS

The data analysis will be carried out with the statistical program IBM SPSS for Windows, version 24.0. Armonk, NY: IBM Corp.

The sample size calculation will be carried out based on the results of a previous pilot study.

The comparison of the results obtained between the Intervention group and the Control group before and after the intervention will be carried out using a mixed factorial model (Split-plot). The intra-subject factor will be time (PRE, POST, POST1). The inter-subject factor will be the group, with two levels: Intervention and Control.

A 95% confidence interval will be considered for the difference and statistical significance will be established at p <0.05.

REFERENCES

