**Design**

The study is presented as a randomized controlled trial, an experimental scientific procedure characterized by the random distribution of the members of a suitable population group into an intervention group and a control group, comparing a specific impact between the groups after a period established in advance.

Its design is a pre-post, based on the measurement and comparison of the variables to be studied before and after the exposure of the participants to the experimental intervention.

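### Baseline is a level of the repeated factor rather than a covariate, and no deciding term is named; adjusting for baseline would recover precision at no cost when visits correlate modestly

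*Protocol*

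**What the plan says.** The Statistical Analysis section fixes three things: the model, its within-subject factor and its between-subject factor. The arm comparison "will be carried out using a mixed factorial model (Split-plot). The intra-subject factor will be time (PRE, POST, POST1", so the within-subject factor has three levels. The between-subject factor has two: "The inter-subject factor will be the group, with two levels: Intervention and Control". The criterion is that "statistical significance will be established at p <0.05", with a 95% confidence interval for the difference. The software is SPSS 24, with no procedure named.

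Under Outcome measures, the visit schedule is "All variables will be evaluated at 3 different times: pre-intervention, immediate post-intervention and one year follow-up". The Design section states random allocation and adds: "Its design is a pre-post, based on the measurement and comparison of the variables to be studied before and after".

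The section names no baseline covariate, no deciding term or contrast, and no single visit as the main one. It gives no sample size, effect size, SD, between-visit correlation or dropout rate; the sample size is to come from a pilot study.

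**The concern.** With PRE as a level of time, the model offers the reader three between-arm results, and none of them is the most precise available.

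- The **group main effect** averages in a visit made before any training. Randomisation makes the expected difference at that visit zero.
- The **group-by-time interaction** spreads the question over 2 degrees of freedom. It says that the arms' profiles differ, but not when or by how much.
- The **contrasts of POST or POST1 against PRE** are differences in change scores. These use the baseline value less efficiently than adjustment for it.

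At stake are the precision of the between-arm estimate and a clear rule for which result is the answer. There is also a conditional point. If the model is run as SPSS repeated-measures GLM, a patient without the one-year visit is dropped altogether, so the POST comparison loses that patient as well.

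**Working it through.** The plan states no figure that could be reproduced, so the check is algebra plus an illustration.

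**Inputs from the protocol:** two randomised arms; visits PRE, POST and POST1; significance at 0.05 (taken as two-sided because of the 95% interval).

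**Assumed, because the protocol gives none:** n = 30 per arm, 1:1 allocation, SD 1 at every visit, the same correlation r between any two visits (compound symmetry), true arm differences (0, d, d) with d = 0.6 SD, complete data.

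**1. Group main effect.** Its expectation is the mean of the three visit differences.
- Effect held at both later visits: (0 + d + d)/3 = 2d/3.
- Effect halved by one year: (0 + d + d/2)/3 = d/2.
- Effect at POST only: (0 + d + 0)/3 = d/3.

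These fractions need no sample size or SD.

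**2. Variance of the POST contrast.** The change score has variance factor 2(1 − r); baseline adjustment has 1 − r². The ratio is 2(1 − r)/(1 − r²) = 2/(1 + r):
- r = 0.3: 2/1.3 = 1.54
- r = 0.5: 2/1.5 = 1.33
- r = 0.7: 2/1.7 = 1.18
- r = 0.8: 2/1.8 = 1.11

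**3. Power.** Noncentrality parameters, with n/2 = 15 and d² = 0.36:
- Interaction: 15 × Σ(difference − mean)²/(1 − r). The differences 0, 0.6, 0.6 have mean 0.4, so the sum is 0.16 + 0.04 + 0.04 = 0.24 and the parameter is 3.6/(1 − r), on 2 and 116 df.
- Change score at POST: 15 × 0.36/[2(1 − r)] = 2.7/(1 − r), on 1 and 58 df.
- Baseline-adjusted POST: 15 × 0.36/(1 − r²) = 5.4/(1 − r²), on 1 and 57 df.

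Power from the noncentral F distribution:

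| r | Interaction (2 df) | Change score at POST | Baseline-adjusted POST |
| --- | --- | --- | --- |
| 0.3 | 50.5% | 48.9% | 66.8% |
| 0.5 | 65.6% | 62.8% | 75.1% |
| 0.7 | 87.4% | 83.9% | 89.2% |
| 0.8 | 97.1% | 95.1% | 96.8% |

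At r = 0.8 the interaction matches the adjusted POST contrast. For the single POST contrast, adjustment still beats the change score, but by less than two points.

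**4. Effect on the pending sample size.** The normal-approximation formula 2 × (1.96 + 0.84)² × variance factor/d², with an assumed d = 0.5 SD and 80% power, gives these numbers per arm for the change score against baseline adjustment: 88 against 58 (r = 0.3), 63 against 48 (0.5), 38 against 33 (0.7), 26 against 23 (0.8).

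**The case against.** A split-plot analysis of a randomised trial with complete data is valid. The interaction belongs to a factorial model by definition, and comparing the arms before and after training is naturally an interaction question. The sample size is still open and could be set for whichever test is kept. All of this stands, and it limits the point to efficiency and clarity.

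Four stronger readings are tempting, and the protocol does not support them.

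- **That the trial's effect will be diluted to two thirds.** A reader might infer this because group is the only between-arm term listed. The protocol does not make the main effect the deciding test, and the interaction is not diluted.
- **That patients missing the one-year visit will be deleted, with bias.** This is so only under repeated-measures GLM. No procedure or missing-data rule is stated, a likelihood-based fit of the same factors would keep partial data, and a SAP commonly settles the matter. Suppose 25% were lost and deleted: 30 × 0.75 = 22.5 per arm. At r = 0.5 the interaction would have 52.2% power against 75.1% for an adjusted POST analysis that keeps everyone. At that same reduced size, baseline adjustment has 62.2%. So 75.1 − 62.2 = 12.9 of the 22.9 points come from the assumed deletion and not from the role of baseline.
- **That the sections conflict on visits.** The Design section speaks of before and after; Outcome measures and Statistical Analysis list the same three times. These are compatible.
- **That risk level must enter the model.** The aerobic modality is one "which will be established depending on the risk stratification of the patient", but a risk covariate is an optional choice and no part of this defect.

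**Conclusion.** The point holds as an improvement. The protocol does fix baseline as an outcome level, so this is more than missing detail, and it leaves the deciding term unnamed. The two-thirds, one-half and one-third fractions apply only if the group main effect is read as the answer. The variance penalty of 2/(1 + r) for contrasts against PRE assumes equal variances across visits.

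The size of the power loss cannot be known from the protocol. On the assumptions above, the interaction falls short of the adjusted POST contrast by about 16 points at r = 0.3, about 10 at 0.5 and about 2 at 0.7, and by nothing at 0.8. To say that the planned model discards power without condition would be too strong. The loss is material only if visits correlate modestly, which the pilot data could show. Loss of POST data through a missed one-year visit is a conditional risk, not something that the protocol states. None of this makes the planned analysis invalid, and it is not a must-fix.

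**What to change.** For outcomes that can reasonably be treated as continuous, replace the split-plot model with a linear mixed model (SPSS MIXED, the same software):

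- outcomes: POST and POST1;
- fixed effects: arm, visit, arm-by-visit, PRE value and PRE-by-visit;
- analysis set: all randomised patients with any post-baseline value;
- result: the adjusted arm difference with its 95% confidence interval at each visit.

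State in advance which visit is the main contrast. POST fits the pre-post design, but the choice is the sponsor's. Averaging the two visits instead would dilute an effect present only at POST. Then base the pending sample size on the named contrast, with the between-visit correlation taken from the pilot study.

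The evaluator-scored quarter squat and the five-item sexual health questionnaire may need a different model; say so where they are analysed. The mixed model still assumes that missing visits are missing at random.

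The cost is one paragraph of protocol or SAP wording. No new data, visits or patients are needed, since the baseline value is already collected.

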Despite the fact that the bulk of the evidence on the benefit of this type of work is in the world of sport due to its importance in preventing injuries and improving control and proprioception of the joint segments, other studies are testing the effectiveness of this work for other populations^29,30^. For example, the GLA: DTM program, a neuromuscular training program run by physiotherapists throughout Denmark is being carried out to improve the symptoms caused by hip osteoarthritis in adult and elderly populations. However, its authors point out the need to study the potential of this type of work not only in pathologies of neuromuscular etiology, but also in other chronic or supervening diseases and in the ability to improve the general condition of the patient^31^. For this reason, we propose this study to know the possible benefits of this work compared to a traditional force protocol.

OBJECTIVES

The general objective of the study is based on verifying whether neuromuscular training is more effective compared to the classic strength training of Cardiac Rehabilitation Programs to improve the functional capacities in patients after acute myocardial infarction.

The specific objectives of this project are:

- Analyze the effect of the intervention on functional parameters of lower limbs

- Determine the effect of the program on variables of strength of respiratory and peripheral muscles

- Analyze the impact of a cardiac rehabilitation program on the quality of life of patients who have suffered an AMI

- Determine the variables that influence the sexual activity of patients after AMI and the impact on their quality of life

METHODS

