ANNEX II. STRENGTH TRAINING PHASE

Classic strength training

| LEVEL | EXERCISE | DOSAGE |
| --- | --- | --- |
| LEVEL 01 | - Hip F/Ext in supine Theraband: 15rep each leg - Hip Ext in Bipe Theraband: 12rep each leg - Bíceps in BipeTheraband: 15rep each leg - Tríceps in BipeTheraband: 15rep each leg | *20’ Exercises*  *TABATA 3 series*  *20’’ rest between exercises*  *60’’ rest between exercises* |
| LEVEL 02 | - Squats in Bipe: 15rep - Weighted Hip Ext in prone: 12rep each leg - Bíceps en BipeTheraband (+): 15rep each leg - Tríceps en BipeTheraband (+): 15rep each leg | *20’ Exercises*  *TABATA 3 series*  *20’’ rest between exercises*  *60’’ rest between exercises* |
| LEVEL 03 | - Static lunge in Bipe: 12rep each leg - Monster-walk Theraband: 30’’ each leg - Abdominales Sahrmann (nivel 1-2) - Plank in prone: 30’’ | *20’ Exercises*  *TABATA 3 series*  *20’’ rest between exercises*  *60’’ rest between exercises* |
| LEVEL 04 | - Weighted Lunge: 12rep each leg - Monster-walk Theraband (+): 30’’ each leg - Abdominales Sahrmann (nivel 2-3) - Plank in prone raising leg: 30’’ | *20’ Exercises*  *TABATA 3 series*  *20’’ rest between exercises*  *60’’ rest between exercises* |

Neuromuscular strength training

| LEVEL | EXERCISE | DOSAGE |
| --- | --- | --- |
| LEVEL 01 | - Assisted quarter squat: 15 rep - Unmodified gluteal bridge: 12 rep - Bilateral assisted upper limb flexión: 15 rep - Standing on BOSU: 30 “ 2 rep | *20’ Exercises*  *TABATA 3 series*  *20’’ rest between exercises*  *60’’ rest between exercises* |
| LEVEL 02 | - Non-assisted quarter squat: 15 rep - Modified gluteal bridge:12 rep - Unilateral upper limb flexión: 12 rep - Standing on air cushion: 30 “ 2 rep | *20’ Exercises*  *TABATA 3 series*  *20’’ rest between exercises*  *60’’ rest between exercises* |
| LEVEL 03 | - Lunge on BOSU: 12 rep each leg - Pivot agains resistance (gluteus medius): 12 rep each leg - Abdominal with upper limb disociation: 25 rep - Lateral Step: 12 rep each leg | *20’ Exercises*  *TABATA 3 series*  *20’’ rest between exercises*  *60’’ rest between exercises* |
| LEVEL 04 | - Weighted Hip Flexo- extensión: 12 rep each leg - Starsexcursion test: 30” each leg - Abdominal control on Bobath ball: 30” 2 rep - Modified weighted stair climb: 15 rep | *20’ Exercises*  *TABATA 3 series*  *20’’ rest between exercises*  *60’’ rest between exercises* |

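### No primary outcome or time is named for the claim on functional capacities; with four to seven eligible tests at p<0.05, the chance of a false-positive difference is about 19% to 30% if the tests are independent.

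*Protocol*

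**What the plan says.** The Objectives section sets the general aim as "verifying whether neuromuscular training is more effective compared to the classic strength training of Cardiac Rehabilitation Programs to improve the functional capacities". This names a domain, not a measurement.

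Outcome measures lists cardiopulmonary exercise testing, ejection fraction, a biochemical panel, the Incremental Shuttle Walking Test (ISWT), four tests under the heading Functional capacities (30-second sit-to-stand, monopodal quarter squat, hip extensor dynamometry, Chester Step Test), two maximal respiratory pressures (PIM and PEM), EQ-5D and a male sexual-function questionnaire. On timing it says: "All variables will be evaluated at 3 different times: pre-intervention, immediate post-intervention and one year follow-up". No variable and no visit is given priority.

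Statistical Analysis describes a split-plot model with time (PRE, POST, POST1) and group as factors, then states: "A 95% confidence interval will be considered for the difference and statistical significance will be established at p <0.05". The sample size is to come from a pilot study, and the outcome that drives it is not stated.

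Annex II lists the exercises of the two strength programmes. They include "Non-assisted quarter squat: 15 rep" in the neuromuscular programme. The related outcome is described as: "Monopodal quarter squat. The subject is asked to flex the knee in single leg stance. The evaluator scores performance".

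**The concern.** A superiority claim needs a defined test. Here the claim concerns a family of tests, each judged at 5%, and nothing says which test or visit decides it. The person writing the results could point to whichever functional test is significant, so the nominal error rate no longer describes the headline conclusion.

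A multiplicity method can reasonably wait for a statistical analysis plan. The primary outcome and time cannot, because they define the trial's question and because no sample size can be derived from the pilot until they are chosen.

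The outcomes are also not interchangeable. Some resemble exercises given mainly to one arm, so a choice made after the results could present practice of a task as a general gain in function.

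**Working it through.** The protocol states no family-wise error rate or power, so there is no figure of its own to reproduce.

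**Inputs**
- Threshold: 0.05 per variable (Statistical Analysis). Sidedness is not stated. The 95% interval implies two-sided testing, hence 0.025 per test in the neuromuscular direction.
- Narrow family: 4, the tests under Functional capacities.
- Wider family: 7, adding ISWT, PIM and PEM. The introduction to Outcome measures groups pressures, shuttle test, strength and lower-limb parameters as the respiratory and functional capacities assessed at the university.
- Assumptions: no true effect, one test per outcome, independent tests.

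**Formulas:** any false-positive difference, 1 − 0.95^k; false win for neuromuscular training, 1 − 0.975^k.

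| k | Any false positive | Favouring neuromuscular training |
|---|---|---|
| 4 | 1 − 0.95^4 = 18.5% | 1 − 0.975^4 = 9.6% |
| 7 | 1 − 0.95^7 = 30.2% | 1 − 0.975^7 = 16.2% |
| One primary test | 5% | 2.5% |

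**Effect of correlation** (four tests, one test per outcome, simulated normal statistics, assumed common correlation)

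| Correlation | Any | Favouring neuromuscular training |
|---|---|---|
| 0.3 | about 17% | about 9% |
| 0.5 | about 16% | about 8% |
| 0.7 | about 13% | about 7% |

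**Effect of testing POST and POST1 separately.** The protocol does not name the contrast taken from the split-plot model. A single group-by-time test gives one test per outcome, as above. Separate tests at each visit double the count. With full independence, four outcomes become 8 tests (33.7% any, 18.3% favouring neuromuscular training) and seven become 14 (51.2% and 29.8%). For four outcomes with assumed correlation 0.7 both between outcomes and between visits, the figures are 20.7% and 10.3%.

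**Overlap between outcomes and training (Annex II)**

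| Outcome | Neuromuscular programme | Classic programme |
|---|---|---|
| Chester Step Test | lateral step (Level 03), weighted stair climb (Level 04) | no step exercise |
| Monopodal quarter squat | quarter squat by name (Levels 01-02), not stated to be single-leg; lunge on BOSU (Level 03) | squats (Level 02), lunges (Levels 03-04) |
| Hip extensor strength | gluteal bridges (Levels 01-02), weighted hip flexion-extension (Level 04) | hip extension (Levels 01-02) |

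Stepping is therefore exclusive to one arm, the quarter squat is partly so, and hip extension is trained in both. Respiratory exercises belong to the warm-up in the session structure, not to either strength programme.

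**The case against.** The strongest reply is that the protocol never says a single significant result establishes superiority. It gives only a threshold and an interval, and an unseen analysis plan may contain a hierarchy and an adjustment. The first part is correct: the percentages are the chance that at least one functional test is available to support the claim, not the chance that the sponsor will make it. But the protocol offers no other rule for reaching its general objective. The absence of an adjustment method is not the point here; the missing primary outcome and time is, and that belongs in the protocol.

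Three stronger readings are tempting and should not be adopted.

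- A reader might count every listed variable, about 28, and obtain 1 − 0.95^28 = 76%. The stated claim is about functional capacities. Twelve laboratory values, ejection fraction, six EQ-5D scores and the sexual-function score (20 of the 28) cannot support it, and exercise testing is introduced with the risk-stratification tests. On the relevant family a false win for neuromuscular training is well above nominal, but it is not likely.
- A reader might infer that several outcomes are rehearsed by one arm only. Annex II contradicts this for squatting and hip extension. Moreover, any extra hip-extension work in the classic programme would favour the control arm.
- The Design section speaks of "comparing a specific impact between the groups after a period established in advance", which could be read as a broken promise of one endpoint. The phrase is part of a general definition of a randomised trial, so it is weak evidence of a contradiction.

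**Conclusion.** The point holds in limited form. The protocol seeks a superiority claim on a family of functional tests, fixes neither a primary outcome nor a primary time, and applies an unadjusted 5% threshold to each variable. With one independent test per outcome and no true effect, the chance of at least one false-positive difference is about 19% (four tests) to 30% (seven). The chance of a false win for neuromuscular training is about 10% to 16% against 2.5%, roughly four to six times nominal (9.6/2.5 = 3.8; 16.2/2.5 = 6.5). Positive correlation lowers these figures, but in the four-test case they stay above nominal even at correlation 0.7. Separate testing at POST and POST1 raises them.

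The training overlap is a secondary reason to choose the outcome in advance. It is clear for the Chester Step Test and partial for the evaluator-scored quarter squat. The documents do not support extending it to the other functional tests.

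**What to change.** Before any between-group data are seen, amend the protocol as follows:

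- Name one functional outcome at the immediate post-intervention visit as primary, and say that the general objective will be judged on it.
- Test its group difference once at two-sided 0.05, and base the pilot-derived sample size on that same contrast.
- Report the remaining functional tests as secondary with Holm adjustment. If ISWT is primary and the wider family is kept, six remain, and the smallest p-value is compared with 0.05/6 = 0.0083.
- Treat POST1, laboratory, ejection fraction, EQ-5D and sexual-function results as supportive, with 95% confidence intervals.

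ISWT distance is one candidate: neither Annex II programme practises it preferentially, and the protocol links it to maximum VO2. It is only an example. It lies outside the Functional capacities heading, and because the arms differ only in the 20-minute strength phase it may be insensitive to the contrast. Another functional test that neither programme practises preferentially would serve.

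The cost is a change of wording. The downside is that some nominally significant secondary results can no longer be claimed as confirmatory.
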